#### Patient Enrollment

A cardiovascular physician will confirm the diagnosis of interested participants based on the 24-h ABPM test (A&D Co. Ltd., Japan TM-2430). A clinical research coordinator (CRC) will screen the participant based on the eligibility criteria, and pre-consent for a physical examination and eligibility laboratory tests. The eligibility of an individual who is deemed potentially eligible per CRC will be further confirmed by a study physician. The CRC will consent and register the participant under the patient information system at the Geriatric Hospital of Sichuan Province.

### Randomization

An independent researcher who will not be involved in contact with patients generates the random sequence in R (28). Each random sequence digit will be sealed in an opaque envelope by a CRC. The acupuncture practitioner opens the sealed envelope to learn the group allocation of a participant before the delivery of the initial acupuncture session.

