### Blinding

All the participants, outcome assessors, and biostatisticians will be masked to group allocation during the study period. Although acupuncture practitioners will not be masked in this trial, they are not involved in any process of outcome assessment. Furthermore, all treatment sessions and outcome assessments will be conducted in a quiet, separate room for each patient to restrict communications between participants and ensure subject blinding. During treatment, patients will be instructed by acupuncture to lie in a supine position and be covered by a light blanket to enhance blinding.

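### One role, the clinical research coordinator, both seals the allocation envelopes and enrols patients, and the protocol does not separate the persons, so concealment from enrolling staff is not assured

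*Protocol article*

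**What the plan says.** The Randomization section of the protocol article describes three steps. A researcher who is independent of the trial's patient contact produces the sequence in R. Then: "Each random sequence digit will be sealed in an opaque envelope by a CRC". Finally, "The acupuncture practitioner opens the sealed envelope to learn the group allocation of a participant before the delivery of the initial acupuncture session".

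The Patient Enrollment section describes who brings patients into the trial. A cardiovascular physician confirms the diagnosis from 24-hour ambulatory monitoring. Then "A clinical research coordinator (CRC) will screen the participant based on the eligibility criteria", and the coordinator also takes a preliminary consent for the examination and laboratory tests. Next, "The eligibility of an individual who is deemed potentially eligible per CRC will be further confirmed by a study physician". Last, "The CRC will consent and register the participant under the patient information system at the Geriatric Hospital of Sichuan Province".

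The Blinding section lists who is kept unaware of the allocation: "All the participants, outcome assessors, and biostatisticians will be masked to group allocation during the study period". Coordinators are not on that list.

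**The concern.** Allocation concealment means that those who decide whether and when a patient enters cannot know the next assignment. The protocol sets up this protection by giving sequence generation to someone without patient contact. It then passes the individual allocations, still unsealed, to a role that screens and consents.

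A coordinator who knew or could recall upcoming assignments could bring a patient forward, hold one back, or judge a borderline case differently, without any intent to do so. The arms would then differ before treatment begins. Masking after allocation does not undo such a difference. The planned mixed-effects model includes the baseline outcome, so it would correct for imbalance in baseline blood pressure but not for imbalance in unmeasured prognosis. What is at stake is whether the acupuncture and sham arms, planned at 32 patients each, are comparable at entry.

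**Working it through.** No arithmetic applies: the point concerns who holds the allocations and does not depend on sample size, power or significance level. The check is to set the stated roles side by side.

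| Step | Who does it | Where stated |
|---|---|---|
| Generate the sequence | Independent researcher, no patient contact | Randomization |
| Seal each allocation in an envelope | A CRC | Randomization |
| Confirm the diagnosis | Cardiovascular physician | Patient Enrollment |
| Screen; preliminary consent for tests | A CRC | Patient Enrollment |
| Confirm eligibility | Study physician | Patient Enrollment |
| Consent and register | The CRC | Patient Enrollment |
| Open the envelope | Acupuncture practitioner | Randomization |
| Masked to allocation | Participants, outcome assessors, biostatisticians | Blinding |

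1. **The role overlaps.** The abbreviation is defined once, under Patient Enrollment, and reused under Randomization. The same role appears on both sides of the barrier that concealment should form.

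2. **The persons are not separated.** No sentence says that the sealing coordinator takes no part in enrolment. No sentence says that it is the same individual either.

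3. **The other safeguards act elsewhere.**
   - *Study physician.* This check covers only patients whom the coordinator has put forward. A patient whom the coordinator declines or delays does not reach it.
   - *Diagnosis check.* It establishes hypertension and has no bearing on who knows the allocation.
   - *Opaque envelopes opened by the practitioner.* These protect against people who did not fill the envelopes, not against the person who did.
   - *Timing.* Table 1 places eligibility and consent at week -1 and random allocation at week 0. That order stops anyone learning an assignment by opening an envelope before consent. It does not help if the assignment was seen at sealing.
   - *Masking.* It omits coordinators and in any case acts after selection has taken place.

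4. **There is room for discretion.** Several exclusion criteria, such as serious primary disease or an abnormal laboratory result, call for judgement, and the interval before allocation leaves the order of entry open to influence.

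**The case against.** The strongest reply is that a shared job title is not a shared person. Both sections introduce the coordinator with an indefinite article, so the site may well use one coordinator for envelopes and another for recruitment. This stands. A reader might infer that allocation is known to the person who enrols, but the documents do not establish that; they only fail to exclude it.

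A second reply is that the coordinator does not control enrolment. This stands too: two physicians have a say, and a reading in which the coordinator alone decides who enters goes beyond the text. The coordinator nevertheless screens before the eligibility check and obtains the final consent, so influence over entry and timing remains.

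A third reply is that filling envelopes is not the same as knowing the list. The article does not say in what order the digits are sealed or whether a list is kept, and foreknowledge is of use only if it is retained and matched to arriving patients. It would therefore be wrong to infer that all 64 assignments are known in advance. The exposure exists; its extent is unknown.

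It might also be said that a condensed article leaves such detail to the full protocol. That reply does not hold here. The article does not omit who seals the envelopes; it names a role, and that role also enrols.

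**Conclusion.** The point holds in a limited form: as written, the protocol gives one role both the sealing of allocations and the screening, consent and registration of patients, without separating the persons, so concealment from enrolling staff is not assured. It does not show that concealment has failed.

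The arrangement covers all 64 randomized patients, but the documents contain nothing from which a bias in mmHg could be calculated, and none should be attached to it. The conclusion rests on two readings: that the abbreviation has the same meaning in both sections, and that a person who seals an allocation can see it. It would fall away if the sponsor states that the sealing coordinator has no part in enrolment. It deserves action because lost concealment cannot be reliably repaired in the analysis, while the remedy is cheap.

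**What to change.** In the Randomization section, replace the coordinator with the independent researcher as the person who prepares and seals the opaque envelopes. Add a sentence that no one who screens, consents or registers patients handles unsealed allocations. This needs no extra staff, since that researcher already holds the sequence and already has no patient contact.

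The Discussions section describes the trial as ongoing, so envelopes may already be sealed. In that case a change of wording alone would not alter who has seen the allocations. The sponsor should then:

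- document who sealed the envelopes and whether that person enrols patients;
- if different people did the two tasks, say so in the protocol, which settles the matter;
- if one person did both, either have the independent researcher re-prepare the unused envelopes or bar the sealing coordinator from further enrolment.

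The cost is a sentence or two of text and, in the last case, a small amount of re-preparation or a change in staff duties.

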### Blinding

All the participants, outcome assessors, and biostatisticians will be masked to group allocation during the study period. Although acupuncture practitioners will not be masked in this trial, they are not involved in any process of outcome assessment. Furthermore, all treatment sessions and outcome assessments will be conducted in a quiet, separate room for each patient to restrict communications between participants and ensure subject blinding. During treatment, patients will be instructed by acupuncture to lie in a supine position and be covered by a light blanket to enhance blinding.

### Interventions

Participants in both groups will receive 10 sessions of acupuncture treatment throughout 4 weeks, three times per week for weeks 1 and 2, and twice per week for weeks 3 and 4. The treatment protocol was developed by consensus with experienced acupuncture physicians and based on our previous studies (20, 25, 29, 30) (Figure 2; ppendix Table 1). All acupuncturists in this trial are registered Chinese Medicine practitioners in China and with at least 3 years of clinical experience in acupuncture practice. Before taking part in this study, all acupuncturists will be required to complete a 40-h standard training course to master the study protocol. When finished, acupuncturists will be required to take an examination to recite the protocol verbally and provide a demonstration of each technique.

**Figure 2 F2:**
[figure not shown]
Acupoints Location, acupuncture intervention and sham-acupuncture intervention.

#### Acupuncture Intervention

Patients in the acupuncture group will receive electroacupuncture treatment. Sterile disposable acupuncture needles (0.18 × 25 mm, 0.18 × 30 mm; Zhongyan Taihe Medical Instrument Co., Ltd., Beijing, China) will be used for treatment. The manipulations are as follows: Acupuncture needles will be inserted into acupoints at a depth of 20-25 mm after skin disinfection using an alcohol wipe. After insertion, needles will be manually manipulated by gentle lifting, thrusting, and rotating until to achieve the *de-qi* sensation. We will use Hwato therapeutic apparatus (Hwato SDZ-II Acupoint Nerve Stimulator, Suzhou Medical Co., Ltd.) to connect the needles at the two acupoints located in the ipsilateral limb. The frequency will be 60/100 Hz, and the electric current will vary from 1.0 to 2.0 mA until the patients feel comfortable. The acupuncture needles will be retained for 25 min in each session. In addition, all participants will receive lifestyle education on how to improve blood pressure through diet, weight control, and exercise.

#### Sham Acupuncture Intervention

Patients in the sham acupuncture group will receive a non-invasive sham acupuncture treatment (31). Acupuncturists will apply a plastic needle guiding tube on the same acupoints in the arm and leg and flick it to produce some discernible sensation; then, a needle with a piece of adhesive tape will be affixed immediately without skin penetration. We will connect the taped needles with a mock transcutaneous electrical stimulation unit (Hwato SDZ-II Acupoint Nerve Stimulator, Suzhou Medical Co., Ltd.), which will emit a sound and possess a blinking light as the acupuncture group but without any electrical stimulation, for 25 min in each session. The sham treatment will be scheduled at the same course and frequency as the experimental group. Participants in the sham acupuncture group will also receive the same lifestyle education.

### Outcome Measurements

#### Primary Outcome

The primary outcome is the change in mean 24-h systolic and diastolic blood pressure at week 4. The 24-h ABPM is a common and objective measure of blood pressure validated in clinical practice and research, which provides accurate estimates of blood pressure throughout the day (32, 33). We will also measure office blood pressure with a mercury gravity manometer before and after each acupuncture treatment, till 8 weeks.

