## Abstract

Essential hypertension is a polygenic cardiovascular disease that is associated with maladaptive metabolic changes. Acupuncture as a non-pharmacologic intervention is used to lower blood pressure and improve metabolic dysfunction. However, such effects have not been clinically characterized. We will conduct a randomized clinical trial to evaluate the antihypertensive effect of acupuncture among patients with essential hypertension and determine the associated metabolic improvements. This study is a phase II, two-arm, randomized, sham-controlled trial (Trial registration: ChiCTR2100043737), in which biospecimens will be collected for metabolic profiling. A total of 64 patients with a clinical diagnosis of essential hypertension will be randomly assigned to either the acupuncture or the sham acupuncture group in a 1:1 ratio. All participants will receive 10 treatments over 4 weeks, with three sessions per week for the first 2 weeks and two sessions per week for the remaining weeks. The primary outcome is the change of the systolic and diastolic blood pressure measured by the 24-h ambulatory blood pressure monitoring from baseline to 4 weeks. Secondary outcomes include the circadian rhythm of blood pressure, sleep quality measured by the Insomnia Severity Index, cognitive function measured by the Montreal Cognitive Assessment, and others. Fasting blood serum and urine samples will be collected at baseline and 4 weeks for targeted and untargeted metabolomics analysis. We will use the mixed-effects model and other related bioinformatics approaches to analyze the clinical and metabolome data. This metabolomic-based trial will provide important clinical data regarding the efficacy of acupuncture for essential hypertension to better inform evidence-based care delivery for hypertension patients. Moreover, the findings will offer important insights into the mechanism of action of acupuncture for hypertension by revealing its effect on metabolism. The results of this study will be used to inform the design of a statistically powered, multicenter, randomized trial. We will publish the study findings in peer-reviewed journals. The ethical approval of this study has been reviewed and approved by the Sichuan Regional Ethics Review Committee on Traditional Chinese Medicine (ID: 2021KL-006). The outcomes of the trial will be disseminated through peer-reviewed publications.

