### Study Design

This study is a randomized controlled trial conducted at the Chengdu University of Traditional Chinese Medicine and the Geriatric Hospital of Sichuan Province, Chengdu, China. A total of 64 patients with essential hypertension and 10 healthy subjects will be recruited. 64 patients will be randomly allocated in a 1:1 ratio to either the acupuncture or sham acupuncture group. Patients will receive 10 treatments over 4 weeks. The primary outcome is the 24-h average blood pressure measured with 24-h blood pressure monitoring (24-h ABPM) at 4 weeks. Secondary outcomes include blood pressure measured at 8 weeks, the 24-h circadian rhythm of blood pressure, the sleep quality measured by the Insomnia Severity Index (ISI), cognitive function measured by the Montreal Cognitive Assessment (MoCA), TCMBC, health-related quality of life, patient's treatment expectancy, and adverse events. The details of the study design are shown in Figure 1. The timeline of recruitment, interventions, and outcome measurements is shown in Table 1.

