### Sample Size

According to preliminary data from our pilot study, acupuncture was associated with a 9.6-mmHg (δ) greater reduction of 24-h average systolic blood pressure and a 7.7-mmHg greater reduction of 24-h average diastolic blood pressure as compared with sham acupuncture. Conservatively, we hypothesized that acupuncture is associated with a 7.5 mmHg reduction (σ) in 24-h systolic blood pressure compared to sham acupuncture. The significance level was set at 0.05 (α = 0.05, *Z*_α_ = 1.96), and the power of the test was set at 0.9 (1-β = 0.9, *Z*_1−β_ = 1.28). A total of 64 participants will be required in this study (32 in each group), including compensation for an anticipated dropout rate of 20%. Additionally, 10 healthy participants will be recruited as the healthy control group.

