### Statistical Analysis Plan

Clinical data will be analyzed with SPSS 24.0 software (SPSS Inc, Chicago, IL, USA). Continuous variables will be presented as mean and SD or as median and interquartile if they are not normally distributed. The baseline variables will be analyzed by the independent-samples t-test and Mann–Whitney U test, where appropriate. Categorical data will be presented as percentages. We will use the mixed-effects model to compare the effect of acupuncture vs. sham acupuncture on blood pressure from baseline to 4 and 8 weeks. The fixed effects are treatment arm, time, group^*^time interaction, and baseline outcome. For metabolomics data, the multivariate and univariate analysis will be performed in combination to determine the plasma metabolites that distinguish EH patients from a healthy subjects, and metabolites that exhibit significant changes before and after treatment in each treatment arm. We will use the Partial least square discriminant analysis (PLS-DA) in SIMCA-P (version 14.0; Umetrics, Umeå, Sweden) and the MetaboAnalyst (http://www.metaboanalyst.ca/MetaboAnalyst/) to fulfill the identification of differential metabolites between groups. All statistical tests will be two-sided, and statistical significance will be set at 5%.

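### Systolic and diastolic 24-h pressure are jointly primary, each tested at 5%, with only systolic sized and no rule for when the primary outcome is met

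*Protocol article*

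**What the plan says.** The protocol article describes the primary outcome in three places.

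- Abstract: "The primary outcome is the change of the systolic and diastolic blood pressure measured by the 24-h ambulatory blood pressure monitoring". Both pressures are named, and the change runs over the four-week treatment period.
- Study Design: "The primary outcome is the 24-h average blood pressure measured with 24-h blood pressure monitoring (24-h ABPM) at 4 weeks". No component is chosen, and the wording is a level and not a change.
- Primary Outcome: "The primary outcome is the change in mean 24-h systolic and diastolic blood pressure at week 4". Both pressures are named again.

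On error rate, the Statistical Analysis Plan section says: "All statistical tests will be two-sided, and statistical significance will be set at 5" (per cent). It plans a mixed-effects model for blood pressure without saying which component carries the primary test.

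On size, the Sample Size section reports pilot differences for both pressures, 9.6 mmHg systolic and 7.7 mmHg diastolic. It then sets a design hypothesis for one only: a "7.5 mmHg reduction (σ) in 24-h systolic blood pressure compared to sham acupuncture". For that hypothesis "The significance level was set at 0.05" and "the power of the test was set at 0.9", giving 32 patients per group (64 in total) with 20% dropout allowed for. The diastolic pilot figure is not carried into a hypothesis.

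**The concern.** With two primary variables, a trial needs a rule that turns two p-values into one conclusion. The article has two variables, gives each the full 5%, and attaches its power statement to one of them.

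If a significant result on either pressure may be reported as a positive primary outcome, there are two chances of a false positive and the 5% no longer describes the trial. If both must be significant, the 90% describes only one of two conditions for success. The difficulty becomes practical when the results disagree. With systolic significant and diastolic not, or the reverse, the text would allow the trial to be called positive or negative, and the choice could be made after the data are seen.

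**Working it through.** **Inputs from the article.** Two primary variables (Abstract, Primary Outcome). Two-sided 5% for each test (Statistical Analysis Plan). Sizing on systolic pressure with Z values 1.96 and 1.28, 32 per arm and 20% dropout (Sample Size). After dropout, 32 × 0.8 = 25.6, about 26 evaluable per arm.

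**Inputs not in the article, assumed here.** The correlation ρ between the two test statistics, and the power of the diastolic test.

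**1. The plan's own figure.** For two means, n per arm = 2(1.96 + 1.28)² × (SD/difference)².

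- By the symbols (δ = 9.6, σ = 7.5): 2 × 10.4976 × (7.5/9.6)² = 12.8, so 13 per arm. 13/0.8 = 16.25, so 17 per arm, 34 in total.
- With the figures the other way round (difference 7.5, SD 9.6): 2 × 10.4976 × (9.6/7.5)² = 34.4, so 35 per arm. 35/0.8 = 43.75, so 44 per arm, 88 in total.
- Of the variants tried, only one gives 32 per arm. The formula for the total, 4 × 10.4976 × (7.5/9.6)² = 25.6, is used as if it were per arm, and 25.6/0.8 = 32.0.
- If 7.5 mmHg is the difference, as the sentence says, 26 per arm gives 90% power only at an SD of about 8.3 mmHg. The article states no such SD.

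The 64 is therefore not reproduced by a correct use of the stated figures, and the 90% below is taken as stated.

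**2. If either pressure is enough.** Under no effect on either, the chance of at least one significant result is 1 − P(|Z1| < 1.96 and |Z2| < 1.96), with Z1 and Z2 bivariate normal with correlation ρ. At ρ = 0 this is 1 − 0.95² = 0.0975.

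| Assumed ρ | Family-wise error |
|---|---|
| 0 (bound) | 9.75% |
| 0.5 | 9.1% |
| 0.7 | 8.3% |
| 0.8 | 7.8% |
| 0.9 | 7.0% |

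Any correlation below 1 leaves it above 5%.

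**3. If both pressures are required.** P(both significant) ≤ P(systolic significant), so the joint power cannot exceed the systolic power, whatever the correlation. How far below it lies depends on the assumed inputs:

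| Assumed diastolic power | ρ = 0 | ρ = 0.7 | ρ = 0.9 |
|---|---|---|---|
| 90% | 81.0% | 84.7% | 86.9% |
| 80% | 72.0% | 76.9% | 79.1% |

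These are illustrations only. If the symbols are taken literally (difference 9.6, SD 7.5, 26 per arm), systolic power is 99.6%. With a diastolic difference of 7.7 and an assumed SD of 7.5, joint power is then about 96%. That reading contradicts the sentence that makes 7.5 mmHg the hypothesised reduction, but it shows that the article does not determine the loss.

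**4. If systolic is tested first and diastolic only after a significant systolic result.** If there is no systolic effect, any false claim needs a false systolic result first, which has probability 5%. If there is a systolic effect, the only possible false claim is the diastolic one, again at most 5%. The family-wise error is at most 5%, and the systolic power is unchanged at the same sample size.

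**The case against.** The strongest reply is that the article states neither an either-rule nor a both-rule. Its 5% sentence is a general one in a condensed paragraph, and a separate analysis plan, not shown, may set the order. That stands in part: the sentence does not say that one significant pressure makes the trial positive. But the article has itself named two primary variables, given each the full 5%, and sized on one. These are statements that do not fit together as they are, and the choice of primary variable belongs in the protocol.

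A reader might infer that either the 5% or the 90% must be wrong. The documents do not support that. An ordered test, systolic first, keeps both, and sizing on systolic alone is compatible with that order. The article simply does not state it.

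A reader might also infer that the trial's true power is 81% to 87%. That is not supported either. Those figures assume 90% diastolic power, a correlation, and a 90% systolic power that the stated figures do not reproduce.

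Zero correlation is a bound and not an expectation, since both pressures come from the same recording. Finally, the abstract and the Discussion present this as a phase II trial that will inform a larger one. That limits the harm but does not remove it, because the first listed aim is to assess efficacy and the trial is sized at 90% power for it.

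**Conclusion.** The point holds in a limited form. The article has two primary variables, two-sided 5% for each, sizing on systolic only, and no criterion for success.

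- Under an either-rule the family-wise error is above 5%: about 7.0% to 8.3% at assumed correlations of 0.9 to 0.7, and 9.75% at the zero-correlation bound. The direction needs no assumption beyond a correlation below 1; the size rests on the assumed correlation.
- Under a both-rule the stated 90% refers to systolic only and is a ceiling. The size of the loss cannot be derived from the article.

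It should be fixed. Given the preliminary purpose of the trial and the existence of an ordered rule that preserves both stated figures, it is not a critical flaw.

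**What to change.** Before unblinding, and without changing the planned 64 patients:

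1. State that the week-4 change in mean 24-h systolic pressure is tested first at two-sided 5%, and that the change in mean 24-h diastolic pressure is tested at 5% only if systolic is significant. Diastolic may be labelled second in a fixed sequence or first secondary outcome; the error control is the same.
2. State in the Sample Size section that the 90% power refers to the systolic test.
3. Use the same wording in the Abstract, Study Design, Primary Outcome and Statistical Analysis Plan sections.

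The cost is that a diastolic-only effect could not be claimed as a primary success. The trial is registered and the Discussion describes it as under way, so the registered outcome wording may also need an amendment.

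Alternatives exist but cost patients or power. Taking the stated 90% at 64 as given, splitting the level into 2.5% each lowers systolic power to about 84%, and about 76 patients in total would be needed to restore 90%. Requiring both pressures would need about 73 to 79 in total for 90% joint power, assuming equal power for the two tests and a correlation between 0.8 and 0.
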